### AEs

2.13

AEs mean negative effects caused by the treatment. During the study, any abnormal reactions from participants will be reported to the researchers. The occurrence time, side effects, degree, duration and mitigation will be recorded in the CRF.

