### Randomization, allocation concealment and partly double-blind

2.9

Two groups, each one of 92 independent random numbers, will be generated using Excel 2013 software (Microsoft Corporation, Redmond, Washington) by the third party that does not participate in the study, and will be divided by 4. The remainder will be 1 for group A, 2 for group B, 3 for group C and 0 for group D. A, B, C, D are prescribed as diet + drug, diet + placebo, drug and placebo group, respectively. The number of the drug will be reserved and will be encapsulated and stored in opaque envelopes, preserved by the third party. When a patient is enrolled, an envelope with a sequence number on its surface will be passed to the researchers. The researchers and patients will know whether diet is interfered and the drug number only, but not the corresponding drug or placebo group. When the trial is finished, the third party will uncover the blindness. It is difficult to conduct blinding since the diet intervention is a set of dietary principles, rather than specific food, so only drugs are double-blind to reduce the information bias.

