#### Safety outcomes

2.12.4

Safety parameters include AEs and laboratory examinations (BR, LKF).

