### Planned statistical analysis

2.15

Continuous variables will be described as the mean ± standard deviation (SD), median or interquartile range (IQR). The number of cases, frequency, the rate and the constituent ratio will be described by categorical variables. Variance analysis will be used for continuous variables in the baseline data having normal distribution and same variance. Wilcoxon rank sum test or Kruskal–Wallis *H* test will be used for the comparison of differences between groups that are not normally distributed or have uneven variance. Categorical variables will be tested by chi–square test or Fisher exact test. Wilcoxon rank sum test or Kruskal–Wallis *H* test will be used for the number of CSBM per week in primary outcome. Chi–square test or Fisher exact test will be used for percent improvement of each symptom scale score in secondary outcome indicators. The result of 48-h GITT will be analyzed using chi-square or Fisher test. Wilcoxon rank sum test or Kruskal–Wallis *H* test will be used for measurement data in HRAM, while chi-square test or Fisher exact test will be used for counting data. Safety, dietary quality, compliance indicators will be tested by chi-square test or Fisher exact test. Wilcoxon rank sum test or Kruskal–Wallis *H* test will be used to compare the diversity, the relative abundance of bacteria in phylum and genera level between 2 or more groups.^[22]^ Complying with the intent-to-treat (ITT) and per-protocol (PP) principle, all data of the patients randomized and at least 1 assessment (include baseline assessment) will be analyzed. For dropouts and terminations, their missing data will be obtained by last-observation-carried-forward (LOCF) method. All statistical analyses will be performed by SPSS20 software (IBM, Chicago, Illinois), and *P* value <.05 will be considered statistically significant.

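### The AE definition in 2.13 requires a causal link to treatment, so events judged unrelated do not count, and the diet versus no-diet AE comparison can be biased

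*Protocol article*

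**What the plan says.** Section 2.13 (AEs) opens with the definition "AEs mean negative effects caused by the treatment". It continues that during the study "any abnormal reactions from participants will be reported to the researchers", and then that "The occurrence time, side effects, degree, duration and mitigation will be recorded in the CRF".

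Section 2.12.4 makes AEs a safety outcome: "Safety parameters include AEs and laboratory examinations (BR, LKF"). Section 2.15 fixes the test: "Safety, dietary quality, compliance indicators will be tested by chi-square test or Fisher exact test".

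On blinding, section 2.9 says "The researchers and patients will know whether diet is interfered and the drug number only, but not the corresponding drug or placebo group", and explains that the diet cannot readily be masked, "so only drugs are double-blind to reduce the information bias". Section 2.2, on the other hand, has outcomes at baseline, day 14 and day 28 evaluated by researchers who are blind to group.

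The Discussion presents this as the first randomised trial to examine whether the diet works and whether it is safe.

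**The concern.** An adverse event is normally any untoward occurrence after allocation, whatever its cause. Whether treatment caused it is a separate, later judgement. Section 2.13 makes that judgement part of the definition, so an event has to be considered treatment-caused before it belongs to the safety outcome.

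Two things are at stake. First, events judged unrelated fall out of the AE count in every arm. Unexpected harms are the ones most likely to be lost this way, because nobody yet suspects the link. Second, randomisation balances the background rate of all untoward events, but it does not balance opinions about their cause. Where the person forming the opinion knows the allocation, the recorded rate can depend on it. Here the open factor is the diet, and the diet is the intervention whose safety the trial sets out to examine.

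**Working it through.** **The passages side by side**

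- Definition (2.13, first sentence): causality is required.
- Reporting (2.13, second sentence): no causality limit on what participants report.
- Recording (2.13, third sentence): the listed items use a causal term, side effects. Section 2.10 likewise keeps emergency-unblinded cases in an analysis of adverse reactions.
- Outcome and test (2.12.4, 2.15): the AE as defined is the safety parameter, tested by chi-square or Fisher.

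Reporting is broad, but what counts is narrow. The article does not say what happens to a reported event that is judged unrelated; under the definition it is not an AE.

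**Which comparison is exposed**

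- Diet versus no diet: researchers and patients know the allocation (2.9), so attribution can differ.
- Drug versus placebo within a diet stratum: both parties are blind, so knowledge of allocation cannot drive attribution.
- Blood routine and liver and kidney function: measured values, independent of attribution.

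**Illustration of scale**

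The article gives no AE rate, so there is no stated figure to reproduce. Inputs:

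- From the article: four groups of 23 per subtype (4 × 23 = 92), so 23 + 23 = 46 with the diet and 46 without; significance at P < .05.
- Assumed: the pooled 46 versus 46 comparison, a true untoward-event rate *p* equal in both groups, and the proportions of events attributed to treatment, *c*₁ (diet) and *c*₂ (no diet).

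Formulas: recorded rates are *p* × *c*₁ and *p* × *c*₂; the spurious difference is *p* × (*c*₁ − *c*₂). The false-positive rate is the sum of Bin(a; 46, *p c*₁) × Bin(b; 46, *p c*₂) over all tables (a, b) that the uncorrected chi-square test rejects at .05.

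| *c*₁ / *c*₂ | *p* = 10% | *p* = 20% | *p* = 30% |
|---|---|---|---|
| 100% / 100% (all events counted) | 0 points; 0.059 | 0 points; 0.051 | 0 points; 0.050 |
| 60% / 60% | 0 points; 0.057 | 0 points; 0.057 | 0 points; 0.053 |
| 80% / 50% | 3 points; 0.100 | 6 points; 0.146 | 9 points; 0.195 |
| 90% / 40% | 5 points; 0.177 | 10 points; 0.314 | 15 points; 0.454 |

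Example: at *p* = 20%, recorded rates are 20% × 80% = 16% and 20% × 50% = 10%, a difference of 6 points with no true difference.

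Section 2.15 also allows Fisher's exact test, which is conservative at these counts. The same sum over the tables that Fisher's test rejects gives 0.025, 0.082 and 0.127 in the 80% / 50% row, against 0.021, 0.026 and 0.030 when all events are counted. At *p* = 10%, Fisher's test therefore stays below .05 even though the recorded rates are distorted.

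The second row matters: with equal attribution the test keeps roughly its nominal level. The definition alone loses events; bias needs attribution that differs between groups. If attribution were lower in the diet groups, a real diet harm would be masked instead.

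**The case against.** The strongest reply is that 2.13 is loosely worded but intends broad capture: any abnormal reaction is reported, and details then go into the CRF. On that reading nothing is filtered. The reading is possible, and it is why the section is better called inconsistent than a clear filter. It does not rescue the definition, because what is reported to researchers and what counts as an AE are different things, and the second is what 2.12.4 and 2.15 use.

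A reader might infer that staff who know the diet allocation decide causality before an event is counted. The article does not say so. It names no assessor of causality and no time for the judgement, and 2.2 says outcome evaluators are blind to group. Section 2.2 does not settle the matter either: it ties blinded evaluation to set time points, whereas AEs are reported throughout, to researchers who under 2.9 know the diet allocation. The two sections need reconciling.

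A reader might also infer that almost nothing can be an AE in the placebo group without diet. That does not follow. Those participants take a matched powder twice daily, and neither they nor the researchers know it is placebo, so a complaint can be attributed to it just as in the drug group. For the same reason, a large attribution gap between drug and placebo has no support in the article.

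Finally, the article is condensed and the CRF is not shown. The absence of a listed relatedness item is therefore no finding. The stated definition is.

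**Conclusion.** The definition is wrong as stated. Followed literally, it drops events judged unrelated in all four arms and leaves the diet versus no-diet AE comparison open to bias from unequal attribution. The documents support **can bias**, not **does bias**. They do not support extending the concern to drug versus placebo within a diet stratum or to the laboratory parameters.

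The size is unknown. In the illustration, a moderate attribution gap (80% versus 50%) produces a spurious 3 to 9 points and roughly two to four times the nominal false-positive rate under the uncorrected chi-square test, less under Fisher's. This rests on assumed event rates, assumed attribution and a pooled 46 versus 46 comparison. Safety is not the primary outcome and the trial is exploratory, so this should be corrected but does not undermine the design.

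**What to change.** In 2.13, define an AE as any untoward medical occurrence after allocation, whether or not related to treatment, and state that it is captured in the same way in all four arms. Record relatedness as a separate item, judged where possible by someone unaware of the diet allocation. In 2.15, make the all-cause AE rate the safety comparison tested, with related AEs as secondary. Reconcile 2.2 with 2.9 on who is blind to diet.

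The cost is one sentence in the protocol, one CRF item and somewhat more recorded events. The change removes the dependence on attribution. It does not remove differences in how readily participants who know their diet allocation report complaints; that limitation remains and should be acknowledged.

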### Data monitoring and confidentiality

2.14

Researchers will be trained in a unified way before the study to ensure it is performed correctly. Data will be locked in the airtight cabinet and will be entered and checked by double entry into the database established by data administrator using Excel 2013 edition (Microsoft Corporation, Redmond, Washington) for management after completion of the study. An independent statistician will analyze the data while the procedure will be monitored by a third individual. The data of the patients involved in the trial will be confidential and will be used only by scientific research institutes. The publication or reporting of any research findings will not reveal the individual identity.

### Planned statistical analysis

2.15

Continuous variables will be described as the mean ± standard deviation (SD), median or interquartile range (IQR). The number of cases, frequency, the rate and the constituent ratio will be described by categorical variables. Variance analysis will be used for continuous variables in the baseline data having normal distribution and same variance. Wilcoxon rank sum test or Kruskal–Wallis *H* test will be used for the comparison of differences between groups that are not normally distributed or have uneven variance. Categorical variables will be tested by chi–square test or Fisher exact test. Wilcoxon rank sum test or Kruskal–Wallis *H* test will be used for the number of CSBM per week in primary outcome. Chi–square test or Fisher exact test will be used for percent improvement of each symptom scale score in secondary outcome indicators. The result of 48-h GITT will be analyzed using chi-square or Fisher test. Wilcoxon rank sum test or Kruskal–Wallis *H* test will be used for measurement data in HRAM, while chi-square test or Fisher exact test will be used for counting data. Safety, dietary quality, compliance indicators will be tested by chi-square test or Fisher exact test. Wilcoxon rank sum test or Kruskal–Wallis *H* test will be used to compare the diversity, the relative abundance of bacteria in phylum and genera level between 2 or more groups.^[22]^ Complying with the intent-to-treat (ITT) and per-protocol (PP) principle, all data of the patients randomized and at least 1 assessment (include baseline assessment) will be analyzed. For dropouts and terminations, their missing data will be obtained by last-observation-carried-forward (LOCF) method. All statistical analyses will be performed by SPSS20 software (IBM, Chicago, Illinois), and *P* value <.05 will be considered statistically significant.

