## Introduction

1

FC is one of the common functional gastrointestinal disorders that affects a large population around the globe. Prevalence rate of FC varies greatly from 1.9% to 27.2% in North America population with the highest estimates from 12% to 19%;^[1]^ In China, it varies from 6% to 13% for the period of 2010 to 2016.^[2,3]^ Gender, age, diet, education, and neurological diseases are the main influencing factors for FC.^[4,5]^ FC is protracted and prone to recurrence, thus affects patient's quality of life adversely along with increase in overall medical costs.^[6]^

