### Sample size

2.6

Due to the lack of relevant evidence, this is an exploratory study with small sample size. A total of 92 participants for each subtype will be recruited and will be further divided in four sub-groups (23 participants in every sub-group).

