#### Baseline information

2.12.1

Baseline information will include demographic data and clinical data from the participants after allocation. Demographic data includes gender, age, height, weight, nationality, occupation, and education level. Clinical data includes past medical history, drug allergy history, the history of medications used to treat or induce constipation, dietary habits in the past year (see Supplementary Table 3),^[21]^ the primary outcome and secondary outcomes.

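### Baseline variables are tested between randomised arms at P<.05, while the primary outcome is analysed only with tests that cannot use baseline CSBM, sex or age as covariates

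*Protocol article*

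**What the plan says.** All references are to the protocol article.

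- **Baseline tests (2.15 Planned statistical analysis).** For continuous data: "Variance analysis will be used for continuous variables in the baseline data having normal distribution and same variance". Rank tests replace this where normality or equal variance fails. For categorical data: "Categorical variables will be tested by chi–square test or Fisher exact test". One threshold applies throughout: a P "value <.05 will be considered statistically significant".
- **Primary outcome (same section).** A Wilcoxon rank sum or Kruskal–Wallis "test will be used for the number of CSBM per week in primary outcome". The other efficacy tests named are of the same kind or are chi-square or Fisher tests. None takes a covariate.
- **Size (2.6 Sample size).** "A total of 92 participants for each subtype will be recruited", split into four arms with "23 participants in every sub-group". No power calculation is given.
- **Candidate covariates.** The Introduction states: "Gender, age, diet, education, and neurological diseases are the main influencing factors for FC". Section 2.12.1 (Baseline information) collects them: "Demographic data includes gender, age, height, weight, nationality, occupation, and education level". It also records the primary outcome at baseline.
- **Allocation (2.9).** Arms are assigned within each subtype by the remainder of a random number. No stratification by sex or age is described.

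**The concern.** Two choices in 2.15 work against each other. The baseline tests examine a null hypothesis that randomisation makes true, so a small P value reports chance. In arms this small, a large P value does not show that a variable is balanced. Meanwhile the outcome tests cannot use the baseline values that the trial collects, so a chance imbalance in a variable that predicts CSBM stays in the diet comparison.

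At stake are the reading of the baseline table and some precision in the estimated diet effect. The long-run error rate of the primary test is not at stake.

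**Working it through.** **Inputs from the protocol.** 92 per subtype, 4 arms, threshold 0.05 (taken as two-sided; the protocol does not say). Arm size: 92/4 = 23, which reproduces the stated figure.

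**Assumed.** Covariate-outcome correlation ρ from 0.2 to 0.5; a diet effect of 0.8 SD for illustration; the proportion of women. The protocol gives none of these.

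**1. Chance of at least one baseline P<.05 per subtype**, if k tests are independent: 1 − 0.95^k.
- The 7 demographic variables: 1 − 0.95^7 = 0.30.
- 23 variables (7 demographic, 4 history and diet items, CSBM, 2 scales, 3 transit measures, 6 manometry measures): 1 − 0.95^23 = 0.69.

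The second figure is an upper case. The transit rates are linked by construction, and some history items are not single variables.

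**2. What a non-significant test can hide.** The standard error of a standardised difference between two arms is √(2/23) = 0.295 SD. On 44 degrees of freedom, P<.05 needs 2.015 × 0.295 = 0.59 SD. A true difference of 0.5 SD would be detected with only 38–40% power. For sex, with 60% women assumed, two arms differ by 5 or more of 23 (22 percentage points) in 17.5% of allocations, and 71% of those are non-significant by chi-square. With 50–70% women the ranges are 15–18% and 66–71%.

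**3. Effect on the unadjusted comparison, given an imbalance of d SD.** The test statistic shifts by ρd/0.295, and its SD is √(1 − ρ²).
- ρ = 0.3, d = 0.4: the shift in the effect is 0.12 SD, or 0.12/0.295 = 0.41 standard errors. Conditional type I error is 5.8%.
- d = 0.5: conditional type I error is 5.9%, 6.9% and 10.0% at ρ = 0.2, 0.3 and 0.5.

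Averaged over all allocations it remains 5%.

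**4. Power for a 0.8 SD effect, one pair of arms**, normal approximation: Φ(0.8/(0.295√(1 − ρ²)) − 1.96).

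| ρ | Power |
|---|---|
| unadjusted | 77% |
| 0.2 | 79% |
| 0.3 | 81% |
| 0.5 | 88% |

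**5. Cost of the covariates.** The table does not charge for estimating three coefficients. With q = 3 covariates and ν residual degrees of freedom before adjustment, the variance of the adjusted difference grows on average by 1 + q/(ν − q − 1) (normal covariates).
- Two arms only (ν = 44): 1 + 3/40 = 1.075. Net variance ratio (1 − ρ²) × 1.075 = 1.03, 0.98 and 0.81 at ρ = 0.2, 0.3 and 0.5.
- One model over all four arms (ν = 88): 1 + 3/84 = 1.036. Net ratio 0.99, 0.94 and 0.78.

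So at ρ = 0.2 there is essentially no net gain. At 0.3 it is slight to modest, and at 0.5 it is clear. Here ρ is the joint correlation of the three covariates with the outcome.

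**The case against.** **Unadjusted analysis is legitimate, and covariates are often left to an analysis plan.** The first part stands: a rank test after randomisation is valid. The second does not dispose of the point, because 2.15 names the primary tests and those tests cannot take covariates. Replacing them with an adjusted primary analysis means changing what is written.

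**No decision rule is attached to the baseline P values.** This stands. A reader might infer that they will be used to certify comparability or to trigger later adjustment. The protocol does not say so, and removing them changes no efficacy result.

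**The Introduction's sentence concerns influences on functional constipation.** This also stands. A reader might infer that sex and age are established predictors of the change in CSBM over 28 days. The document does not show that. It makes them reasonable candidates. Baseline CSBM is the more obvious covariate and probably the stronger one.

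**The consequence is small and the trial is exploratory.** Largely right, as steps 3 to 5 show. Two stronger readings fail for this reason. One is that the primary comparison is biased or invalid: its overall error stays at 5%. The other is that the baseline table will almost surely contain a false positive: the supportable range is 30% to 69% per subtype.

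**Adjustment is not free.** Agreed. Nor does every adjusted model help. Logistic regression on the responder definition changes the odds ratio being estimated and does not reliably gain precision, so it is not recommended here.

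**Conclusion.** The point holds as a minor, inexpensive improvement. The baseline tests in 2.15 cannot do a useful job: their positives are chance, and between two arms of 23 they are silent below about 0.59 SD. The planned primary test is valid but leaves collected baseline information unused.

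The benefit of adjustment rests on an assumed correlation that the protocol does not supply. It is negligible at 0.2 or less and worthwhile at about 0.3 and above, particularly if one model covers all four arms of a subtype. All power figures assume 23 per arm, an effect of 0.8 SD and approximately normal outcomes.

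**What to change.** In 2.15:

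1. Describe baseline variables by arm, without between-arm P values.
2. For the diet comparison within each subtype, prespecify a covariate-adjusted analysis of CSBM per week: analysis of covariance, or its rank-based form if the counts are skewed. Use baseline CSBM, sex and age as covariates whatever imbalance is observed. Fitting one model to all four arms of a subtype keeps the cost lowest.
3. Keep the planned rank test as a sensitivity analysis.

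Cost: a change of wording, about three degrees of freedom, and a little more analysis work. All three covariates are already collected, so no new data are needed.

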#### Secondary outcomes

2.12.3

*CSS:* The scale for constipation-related symptoms is used for investigating the degree and frequency of symptoms mentioned in Roman IV diagnostic criteria for FC. The degree of discomfort is assessed by visual analog scale (VAS), in which 0 represents no discomfort and 10 represents very strong discomfort. The final scores are obtained with the multiplication of the 2 and then divided by the average number of defecations per week (see Supplementary Table 4). Percent improvement will be calculated as following:
 

Recovery means symptoms disappeared; Marked improvement means percent improvement is more than or equal to 80%; Progress means percent improvement is more than or equal to 50% but less than 80%; Ineffective means percent improvement is less than 50%.

*TCMSS:* The TCMSS is established by collecting information about effects of relevant syndromes of TCM constipation, which are assigned 0, 1, 2, and 3 points representing normal, mild, moderate, and severe degrees, respectively. Normal refers to the absence of this syndrome, mild refers to a slight impact on life, moderate means a significant impact on life and severe refers to the serious impact on life (see Supplementary Table 5). Nimodipine method is used for evaluating the effects of relevant syndromes of TCM constipation.
 

Symptoms, signs disappeared or basically disappeared and syndrome integral reduced more than or equal to 95% is considered clinical cure; Significantly effective means that symptoms, signs significantly have improved and syndrome integral has reduced more than or equal to 70%; Effective means that symptoms, signs have improved and syndrome integral have reduced more than or equal to 30%; Ineffective means that symptoms, signs have no improved or have even aggravated and syndrome score has reduced less than 30%.

*48-h GITT:* 48-h GITT is a simple method for evaluating the function of gastrointestinal motility. The barium residue rate is the ratio of the number of barium remaining in the body 48 hours after swallowing 20 barium bars with a standard meal. Higher residue rate indicates the worse gastrointestinal transport function. The parameters include barium excretion rate after 48-hour, residue rate above rectosigmoid colon and residue rate within rectosigmoid colon. The barium excretion rate in normal people is more than or equal to 90%.

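### Chi-square or Fisher tests are assigned to 48-h GITT rates and to CSS/TCMSS percent improvement, where the plan's own rank tests fit the scale and would keep more power

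*Protocol article*

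**What the plan says.** Section 2.15 (Planned statistical analysis) of the protocol article fixes the tests outcome by outcome.

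- **48-h GITT:** "The result of 48-h GITT will be analyzed using chi-square or Fisher test".
- **CSS and TCMSS:** a chi-square "test or Fisher exact test will be used for percent improvement of each symptom scale score in secondary outcome indicators".
- **Other measured outcomes:** weekly CSBM counts, HRAM measurement data and bacterial diversity and abundance get the Wilcoxon or Kruskal–Wallis test. For HRAM the section separates measurement data (rank tests) from count data (chi-square or Fisher).

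Section 2.12.3 (Secondary outcomes) defines the variables.

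- **48-h GITT:** "The barium residue rate is the ratio of the number of barium remaining in the body 48 hours after swallowing 20 barium bars". Three such quantities are named: "The parameters include barium excretion rate after 48-hour, residue rate above rectosigmoid colon and residue rate within rectosigmoid colon". One reference limit is given, for the excretion rate: "The barium excretion rate in normal people is more than or equal to 90" per cent.
- **CSS:** a percent improvement graded as recovery, marked improvement, progress or ineffective, for example: "Progress means percent improvement is more than or equal to 50% but less than 80" per cent.
- **TCMSS:** a percent reduction graded into four ordered levels, with limits at 95%, 70% and 30%.

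Section 2.6 sets 23 participants in each of four groups per subtype.

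**The concern.** A chi-square or Fisher test compares frequencies across unordered categories. None of these outcomes starts out in that form.

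- Each GITT parameter is a rate per patient that can take 21 values (0 to 20 markers). Only the excretion rate has a limit that would turn it into a patient-level category. For the two regional residue rates, the named test has no table defined in the article.
- CSS and TCMSS improvement is a percentage. It is first cut into four grades, and the test then ignores their order. A significant four-category result need not mean that one group did better.

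The plan applies a different logic to HRAM measurements, which are the same kind of data. What is at stake is mainly power, in a trial whose authors already describe the sample as small.

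**Working it through.** **Inputs from the article:** 23 per group, four groups (2.6), so 4 × 23 = 92, which reproduces the stated total per subtype; 20 markers per patient; four CSS grades with limits at 50% and 80% plus recovery (2.12.3); significance at P < .05 (2.15). The article gives no power figure to reproduce.

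**Assumptions, not from the article:** CSS percent improvement roughly normal with SD 35 and means 50 and 75 in two arms, with recovery taken as 100%; separately, proportional-odds shifts with odds ratios of 3 and 5; within-patient marker correlation of 0.1 to 0.5.

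**1. What grading does to the CSS percentages**

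Grade probabilities under the normal model:

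| Grade | Mean 50 | Mean 75 |
|---|---|---|
| Ineffective (<50%) | Φ(0) = 0.50 | Φ(−0.71) = 0.24 |
| Progress (50 to <80%) | Φ(0.86) − 0.50 = 0.30 | Φ(0.14) − 0.24 = 0.32 |
| Marked (80 to <100%) | Φ(1.43) − 0.80 = 0.12 | Φ(0.71) − 0.56 = 0.21 |
| Recovery (100%) | 0.08 | 0.24 |

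The average cell holds 23/4 = 5.75 patients. Simulated two-arm power at 23 per arm, with a simulation error of about one point:

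| Analysis | Power |
|---|---|
| Chi-square, four unordered grades | about 41% |
| Chi-square, effective/ineffective | about 47% |
| Rank test on the four grades | about 58% |
| Rank test on percent improvement | about 62% |

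Against the rank test on percentages, the loss is 62 − 41 = 21 points on four grades, or 62 − 47 = 15 points on the two-category version.

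**2. A second model for the grades**

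Four ordered grades with a proportional-odds shift, 23 per group, over three assumed baseline distributions. For four groups, two are placed at half the log odds ratio.

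| Groups | Odds ratio | Unordered chi-square | Rank test |
|---|---|---|---|
| 2 | 3 | 0.31–0.36 | 0.48–0.51 |
| 2 | 5 | 0.66–0.69 | 0.83–0.84 |
| 4 | 3 | 0.21–0.22 | 0.34–0.37 |
| 4 | 5 | 0.47–0.48 | 0.68–0.69 |

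The loss is about 14–17 points with two groups and 11–22 with four.

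**3. GITT with the patient as the unit**

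Simulated with no true difference, a chi-square on patients classified by an excretion rate of at least 90% rejects in 0.1% to 5.4% of runs. A rank test on per-patient counts rejects in about 4–6%. Neither inflates the error. The power lost by cutting the GITT rates was not calculated.

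**4. GITT if markers were pooled (conditional)**

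Pooling would give 23 × 20 = 460 markers per arm. With correlation ρ within a patient, the design effect is D = 1 + (20 − 1)ρ, and the true error is P(χ² > critical value / D), with critical values 3.84 for two arms and 7.815 for four.

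| ρ | D | Two arms | Four arms |
|---|---|---|---|
| 0.1 | 2.9 | 0.25 | 0.44 |
| 0.3 | 6.7 | 0.45 | 0.76 |
| 0.5 | 10.5 | 0.55 | 0.86 |

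A beta-binomial simulation agrees. At ρ = 0.01 the two-arm error would be only 0.072.

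**The case against.** A reader might infer that the 20 markers per patient will be pooled and that the GITT p-values are therefore invalid, with false positives about 5 to 11 times too frequent for two arms. The article does not support this. Nothing in it pools markers, uses 460 as a denominator or gives a within-patient correlation. The excretion rate also has a printed normal limit, so a table with one entry per patient is available and holds its error near 5% or below. The missing limits for the regional rates may stand in the full protocol or analysis plan, and their absence from a condensed article does not imply pooling. This objection stands in full against any claim of shown inflation.

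Two further points stand in part.

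- A chi-square on patient-level grades is a valid test, and Fisher's exact test is named as the alternative, so small cells are no defect in themselves. If the grades are collapsed to effective/ineffective, the comparison has a direction and loses less: 58 − 47 = 11 points against a rank test on the grades, rather than 58 − 41 = 17. The article does not say which version is meant. Some loss remains under either.
- These are secondary outcomes in a trial declared exploratory, and the primary CSBM count already has a rank test. This limits the consequence but does not remove the mismatch, because the test is stated in the article and not left to another document.

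**Conclusion.** The point holds as a mismatch between test and scale that costs power. Section 2.15 names categorical tests for per-patient rates and for graded percentages, against its own practice for HRAM measurements.

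For CSS the cost is about 15 to 21 points of power against a rank test on the percentages, under an assumed 25-point shift with SD 35. The article gives no values to check that scenario against. The proportional-odds model supports the direction and rough size of the loss for any scale with four ordered grades, which includes TCMSS. For GITT the loss of information follows from the definitions but is not quantified.

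Inflated error is not shown. It would reach about 25–55% (two arms) or 44–86% (four arms) only if markers were pooled and the within-patient correlation were 0.1–0.5, and both are assumptions. The primary outcome is not affected.

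**What to change.** Amend section 2.15 as follows.

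- State that the patient is the unit of analysis for all GITT results. This also rules out the pooled-marker reading.
- Test each of the three GITT rates, and the CSS and TCMSS percent improvement (or score), with the Wilcoxon or Kruskal–Wallis test already in the plan. A baseline-adjusted analysis is optional.
- Keep the proportion of patients with an excretion rate of at least 90%, and the CSS and TCMSS grades, as supportive results.
- If the grades are tested, use a rank or ordinal test.

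The cost is a few sentences. The planned assessments already supply the data, and neither the sample size nor the conduct of the trial changes.
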